**Figure 1. fig1-1759720X251324429:**
[figure not shown]
Study Design of FASTLANE study.

Digitally collected PROs will include total pain, total back pain, and nocturnal back pain in the last 24 h on days 1–6. From week 1, digitally collected PROs will be collected weekly from weeks 1 to 3, and then at weeks 8 and 12; and will also include BASDAI, nocturnal back pain, and patient global assessment (PtGA) during the last 7 days. PROs at screening (BASDAI, PtGA only), baseline, week 4, and week 16 will be collected during the correspondent face-to-face visit.

Safety will be monitored throughout the whole duration of the study up to 4 weeks after the last study drug dose. A comprehensive cardiovascular (CV) and venous thromboembolism (VTE) risk assessment will be performed at each applicable face-to-face visit to maintain an adequate benefit:risk balance for all study participants. For VTE, subjects will be screened for factors such as heart failure, recent myocardial infarction, inherited coagulation disorders, prior VTE, hormone therapy use, malignancies, major surgery, or immobilization. Additional risk factors including age, obesity, diabetes, hypertension, smoking, and family history of VTE will also be considered. Any newly developed risks will prompt reevaluation and possible treatment discontinuation. Similarly, the CV risk assessment will include evaluation using the Systemic Coronary Risk Estimation 2 calculator, along with other factors like atherosclerotic CV disease, uncontrolled diabetes, smoking history, and family history of premature CV events. Continuous monitoring at each visit will ensure timely management of newly emerging risks, promoting patient safety.

This protocol has been developed using the SPIRIT (Standard Protocol Items: Recommendations for Interventional Trials) 2013 statement, a guideline on standard protocol items for clinical trials.^
28
^ SPIRT Checklist for FASTLANE study is available as Supplementary Material.

### Endpoints

The primary endpoint is the proportion of patients achieving an Axial Spondyloarthritis Disease Activity Score^
29
^ with CRP (ASDAS) <1.3 at week 16.

The key secondary endpoint is the change from baseline in the MRI SIJ SPARCC osteitis score at week 16. Other efficacy secondary endpoints are the proportion of patients achieving (1) ASDAS low disease activity (<2.1) at weeks 4 and 16; (2) ASDAS clinically important improvement (⩾1.1) at weeks 4 and 16; (3) ASDAS major improvement (⩾2.0) at weeks 4 and 16; (4) ASAS20 and ASAS40 response and ASAS partial remission at weeks 4 and 16; (5) BASDAI50 at weeks 4 and 16; (6) change from baseline in ASDAS, Physician Global Assessment, and serum CRP at weeks 4 and 16; and (7) change from baseline in BASDAI and PtGA at weeks 1, 2, 3, 4, 8, 12, and 16. In addition, the efficacy of tofacitinib 5 mg BID versus placebo on achieving early treatment response will be assessed by the proportion of subjects requiring treatment escalation to open-label tofacitinib at week 4. Additional secondary endpoints will include treatment responses on pain reduction (including very early response assessed daily within the first week of treatment), function, mobility, peripheral musculoskeletal manifestations, fatigue, quality of life, and extra-musculoskeletal manifestations at week 16 and at all other applicable time points. Safety secondary endpoints include incidence of adverse events (AEs), AE of special interest, and AEs leading to study discontinuation. Exploratory endpoints are the development of structural changes in the MRI of SIJ by the change from baseline in the SPARCC structural score of the MRI SIJs at week 16, and to assess the efficacy of tofacitinib 5 mg BID versus placebo by subgroup populations. The full list of study endpoints is found in Table 3.

**Table 3. table3-1759720X251324429:** Primary, secondary, and exploratory endpoints of the FASTLANE study.

*Primary endpoint*
Proportion of subjects achieving ASDAS <1.3 at week 16.
*Key secondary endpoint*
Change from baseline in the MRI SIJ SPARCC osteitis score at week 16.
*Other secondary endpoints*
At weeks 4 and 16, the proportion of patients achieved: • an ASDAS clinically important improvement • an ASDAS major improvement • ASDAS <2.1 • ASAS20, ASAS40, ASAS partial remission, BASDAI50 responses At weeks 4 and 16 vs baseline, improvement in disease activity, function, axial mobility, and QoL was measured according to: • ASDAS • BASDAI • PGA • CRP • BASFI • BASMI and chest expansion • 44 TJC/SJC for peripheral involvement • MASES for enthesitis • Dactylitis count • ASAS-HI and FACIT-F The proportion of subjects requiring treatment escalation to open-label tofacitinib at week 4 (proportion of subjects with BASDAI ⩾4 plus BASDAI reduction <20% from baseline at week 4) At weeks 1, 2, 3, 4, 8, 12, and 16 vs baseline, improvement in: • total back pain (NRS) (question 2 of BASDAI) in the last 24 h and 7 days • nocturnal back pain (NRS) in the last 24 h and 7 days • total pain (NRS) in the last 24 h • PtGA At day 1–6 vs baseline, improvement in: • Total back pain (NSR), nocturnal back pain (NSR), and total pain (NSR) in the last 24 h At week 16 vs baseline, improvement in EMMs (overall and by EMM type) At week 20 (or 4 weeks after ET), safety and tolerability of tofacitinib vs placebo by incidence of AEs, TEAEs, AEs of special interest,^ a ^ AEs leading to study discontinuation.
*Tertiary/exploratory endpoints*
At week 16, the proportion of patients achieving ASDAS <1.3 by: • radiographic status (nr-axSpA/r-axSpA) subgroup • CRP (elevated/non-elevated) subgroup • sex subgroup (female/male) • tofacitinib early treatment response subgroup (responders at week 4/non-responders at week 4) At week 16 vs baseline, improvement in MRI SIJ SPARCC structural score.^ b ^ At week 16 vs baseline, improvement in MRI SIJ SPARCC osteitis score by: • radiographic status (nr-axSpA/r-axSpA) subgroup • CRP (elevated/non-elevated) subgroup • sex subgroup (female/male) • tofacitinib early treatment response subgroup (responders at week 4/non-responders at week 4).

a AEs of special interest are: all malignancies excluding NMSC, NMSC, MACE, DVT, PE, ATE, GI perforation, hepatic events, DILI, HZ, OI, OI excluding HZ, SIE, and ILD.

b Components include backfill, fat metaplasia, sclerosis, erosion, and ankylosis.

AE, adverse events; ASAS, Assessment in SpondyloArthritis international Society; ASAS HI, ASAS Health Index; ASDAS, Axial Spondyloarthritis Disease Activity Score; ATE, arterial thromboembolism; BASDAI, Bath Ankylosing Spondylitis Disease Activity Index; BASFI, Bath Ankylosing Spondylitis Functional Index; BASMI, Bath Ankylosing Spondylitis Metrology Index; CRP, C-reactive protein; DILI, drug-induce liver injury; DVT, deep vein thrombosis; EMM, extra-musculoskeletal manifestations; FACIT-F, Functional Assessment of Chronic Illness Therapy- Fatigue; GI, gastrointestinal; HZ, herpes zoster; ILD, interstitial lung disease; MACE, major adverse cardiovascular events; MASES, Maastricht Axial Spondyloarthritis Enthesitis Score; MRI, magnetic resonance imaging; NMSC, non-melanoma skin cancer; nr-axSpA, non-radiographic axial spondyloarthritis; NRS, numerical rating scale; OI, opportunistic infections; PE, pulmonary embolism; PGA, Physician Global Assessment; PtGA, Patient Global Assessment; r-axSpA, radiographic axial spondyloarthritis; SIE, serious infections events; SIJ, sacroiliac joints; SJC, swollen joint count; SPARCC, Spondyloarthritis Research Consortium of Canada; TEAE, treatment-emergent adverse event; TJC, tender joint count.

### Site monitoring and data management

The collection of the data will be done electronically using electronic case report forms (eCRF). At every stage of the data management process, the data collected will be securely stored and patient confidentiality will be always maintained in accordance with data protection laws. Access to the EDC system will be by username/password combination only and available to authorized personnel. When data entry is performed at the investigator site, investigators will not have access to the whole database but only to the data entered by the individual site on their enrolled patients. The patient identification list will remain in the investigator’s file. A trained site monitor will conduct a site initiation visit, regular follow-up with the sites during the study, and a site closeout visit at the end. The site monitor will ensure that local teams and investigators are well-trained in the protocol and address any issues identified. To strengthen the reliability of the data, automatic validation checks will be performed for any irregularities in the eCRF entries and will allow modifications by the investigators until the lock of the database. In addition, the site monitor will conduct source data verification with selected data to detect errors and query inconsistencies.

This study may be audited by the sponsor, the marketing authorization holder of tofacitinib (i.e., Pfizer), any person authorized by the sponsor, or the competent health authority to determine the authenticity of the recorded data and compliance with the study protocol. In addition, changes to the protocol can only be made in a written protocol amendment format, which needs the approval of the sponsor and regulatory authorities before its implementation.

### Sample size

The sample size calculation is based on the primary efficacy endpoint (i.e., the proportion of patients achieving remission defined as ASDAS <1.3 at week 16). The sample size estimation is driven by treatment effect evaluation between an active treatment group and a placebo group. We assumed that tofacitinib (+naproxen) would be at least as effective as infliximab (plus naproxen) in this study population. Based on the results of the INFAST study,^
30
^ we anticipate that 20% in the placebo (+naproxen) group and 50% in the tofacitinib (+naproxen) group will achieve remission (ASDAS <1.3) at week 16. With these assumptions, a total of 104 subjects will be randomly assigned to one of the arms (tofacitinib 5 mg BID or placebo) in a ratio of 1:1 stratified by radiographic status (r-axSpA or nr-axSpA) and CRP status (elevated or non-elevated) to show the difference between the study arms with a power of 90% and two-sided alpha of 0.05. Considering low historical drop-out rates, the sample size will not be adjusted for the drop-out rate.

### Methods against bias

To mitigate bias, patients will undergo randomization during their baseline visit. They will be assigned to receive either tofacitinib 5 mg BID or placebo (both on a background of naproxen 500 mg BID), with assignments following a 1:1 ratio, stratified by radiographic classification (r-axSpA or nr-axSpA) and CRP status (elevated or non-elevated). The study will be conducted in a double-blind fashion to ensure an unbiased assessment of the clinical outcomes. In addition, MRI and X-ray of the SIJ will be assessed centrally by three trained readers (two independent readers, and an additional independent reader in case of disagreement) blinded to all clinical data including treatment allocation as well as to the time points for MRI SIJ image acquisition. Investigators and patients will remain blinded to the original randomization group allocation until the database release.

### Statistical analysis

The unblinded analysis will be performed on all patient data after the last patient has completed week 20 (or the last visit in early termination) and after the study database is locked.

Efficacy analyses will be performed in the modified intent-to-treat population that will be defined as all patients who are randomly assigned to study intervention with the investigational medicinal product (IMP, i.e., tofacitinib or placebo) and who have taken at least one dose of IMP. Participants will be analyzed using the treatment groups as they are randomized.

The primary analysis will focus on the proportion of patients who achieve remission, as defined by ASDAS <1.3 at the end of week 16. For comparison of tofacitinib versus placebo, the Mehrotra and Railkar^
31
^ method will be used, adjusting for the stratification factors (nr-axSpA/r-axSpA and elevated CRP/non-elevated CRP) if sufficient subjects are present in each stratum. Otherwise, the exact Chan and Zhang^
32
^ method will be applied. The difference in the remission rates between treatment groups and the corresponding two-sided 95% confidence interval adjusted for stratification factors will be reported. Missing values from patients who drop out or receive prohibited medication or treatment escalation for any reason before week 16 will be imputed as non-responders. For sensitivity analysis, the above analysis will be repeated using data as observed without missing imputation.

For the key secondary endpoint, change from baseline in MRI SIJ SPARCC osteitis score at week 16 will be analyzed using analysis of covariance adjusting for baseline score and stratification factor (if there are a sufficient number of subjects in each stratum, otherwise stratification factor will be removed from the model) to estimate the effect of initially randomized treatment. The least-squares means and the difference in least-squares means between treatment groups, both with their corresponding 95% confidence intervals will be presented. Data after patients receiving prohibited medicine or treatment escalation will be excluded from the analysis and only observed data will be used (missing data will not be imputed).

For continuous secondary endpoints measured at a single visit, the same analysis as defined in the key secondary endpoint analysis will be repeated. For endpoints with multiple visits, change from baseline over time will be analyzed using the mixed-effect model for repeated measures accounting for fixed effects of baseline score, visit, treatment, treatment-by-visit interaction, and stratification factors (if sufficient patients in each stratum). For sensitivity analysis of key secondary endpoints and secondary continuous endpoints, missing data will be imputed using baseline observation carried forward and the above corresponding analysis will be repeated.

For binary secondary endpoints, the same analysis as defined in primary analysis and corresponding sensitivity analysis will be applied accordingly. Safety analyses will include all patients randomly assigned to study intervention and who take at least one dose of IMP. Participants will be analyzed according to the treatment they have actually received. AEs will be coded using the Medical Dictionary for Regulatory Activities. Safety data will be presented in tabular and/or graphical format and summarized descriptively, where appropriate.

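### One thin stratum removes both randomisation factors from every efficacy model, although the plan promises a stratification-adjusted interval without exception

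*Protocol article*

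**What the plan says.** All references are to the protocol article.

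- **Sample size:** "a total of 104 subjects will be randomly assigned to one of the arms", "in a ratio of 1:1 stratified by radiographic status (r-axSpA or nr-axSpA) and CRP status (elevated or non-elevated"). That is four strata at about 52 patients per arm. The stratification is unconditional and is repeated under Study population and design and under Methods against bias.
- **Statistical analysis, primary endpoint:** the Mehrotra-Railkar method adjusts for both factors "if sufficient subjects are present in each stratum. Otherwise, the exact Chan and Zhang" method applies. The next sentence says that the difference in remission rates and "the corresponding two-sided 95% confidence interval adjusted for stratification factors will be reported", with no exception for the fallback.
- **Statistical analysis, key secondary endpoint:** the ANCOVA adjusts for baseline score and stratification "if there are a sufficient number of subjects in each stratum, otherwise stratification factor will be removed from the model".
- **Statistical analysis, endpoints with several visits:** the repeated-measures model includes "stratification factors (if sufficient patients in each stratum").
- **Statistical analysis, binary secondary endpoints:** these take over the primary rule.

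**The concern.** The rule is all-or-nothing. If one of the four cells is thin, both factors go, including a factor whose own two levels are well filled. The section offers no intermediate step such as pooling cells or keeping one factor.

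Three things follow:

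- The exact Chan-Zhang method is unstratified, so in that branch the promised adjusted interval cannot be produced.
- Stratified randomisation balances the arms on the factors. An analysis that ignores a prognostic factor overstates the variance, so the test becomes conservative and the estimate less precise. CRP enters ASDAS directly and ASDAS defines the primary endpoint, so some prognostic effect of CRP status is plausible.
- For the ANCOVA and the repeated-measures model the condition is the wrong one. Two binary main effects need adequate numbers at each level of each factor, not in each of the four combinations. The key secondary analysis also excludes data after escalation, so its cells are thinner than those of the primary analysis. The rule could therefore fire for one endpoint and not the other.

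**Working it through.** **1. The plan's own figure.** Inputs from Sample size: "we anticipate that 20% in the placebo (+naproxen) group and 50% in the tofacitinib (+naproxen) group will achieve remission", "with a power of 90% and two-sided alpha of 0.05". With pooled variance and no continuity correction, the mean rate is 0.35:

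n per arm = [1.960·√(2·0.35·0.65) + 1.2816·√(0.20·0.80 + 0.50·0.50)]² / 0.30² = (1.322 + 0.821)² / 0.09 ≈ 51.0, rounded up to 52.

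The total is 104, as stated. No credit for stratification was taken.

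**2. Power of the fallback.** The unstratified statistic is z = (p₁ − p₀)/√[p̄(1 − p̄)(1/52 + 1/52)]. By exact enumeration at 52 per arm, the smallest cut-off that holds each one-sided error at 0.025 for every common rate is 1.990. Exact power at 20% against 50% is 90.6%.

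**3. Cost of ignoring the strata, primary endpoint.** Stratum sizes and rates are not in the document, so all of those below are assumptions. The stratified comparator is the Cochran-Mantel-Haenszel (CMH) test, z = Σ(aₕ − Eₕ)/√ΣVₕ over strata. Results are simulated for 10/4/22/16 patients per arm.

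| Assumed setting | Stratified CMH | Chan-Zhang fallback |
|---|---|---|
| Type I error, null rates 28/15/55/18% | 5.0% | 3.5% |
| Type I error, null rates 15/5/45/8% | 5.0% | 3.1% |
| Power, strata not prognostic | 90.8% | 90.5% |
| Power, mild (null rates 20 to 35%) | 91.4% | 90.9% |
| Power, log-odds spread 1.5 | 93.0% | 91.5% |
| Power, log-odds spread 2.5 | 95.5% | 92.8% |

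The power differences are 0.3, 0.5, 1.5 and 2.7 points. The last belongs to an extreme setting, an odds ratio of e^2.5 ≈ 12 between the best and worst strata. In the two type I error settings, the unstratified z at the ordinary 1.96 rejects 3.8% and 3.4% of the time, so there most of the conservatism comes from ignoring the strata.

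With other assumed shares (from 25% each to 3/7/10/80%) and spreads up to 1.8, the loss is 0.2 to 1.4 points. It is 0.2 to 1.0 points where some stratum-by-arm cell is below 5. The fallback's type I error is then 4.2 to 4.8%.

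**4. Interval width, primary endpoint.** Take 26/52 against 10/52 responders. The Chan-Zhang interval is 0.110 to 0.475 (width 0.365), against 0.342 for Miettinen-Nurminen and 0.346 for Wald. The ratios are 0.365/0.342 = 1.07 and 0.365/0.346 = 1.05. None of these intervals is stratified, so this 5 to 7% is the price of exactness. Dropping the strata by itself overstates the standard error by 0 to 3.5%, and by at most about 1.5% when one stratum is very small.

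**5. ANCOVA.** If the factors explain a share R² of the variance left after baseline, dropping them widens the interval by 1/√(1 − R²). An adjusted power of 90% becomes Φ[(1.960 + 1.2816)·√(1 − R²) − 1.960].

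- R² = 5% (assumed): 2.6% wider, power 88.5%.
- R² = 10% (assumed): 5.4% wider, power 86.8%.

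**6. What main effects need.** Let the assumed 10/4/22/16 be r-axSpA with elevated and non-elevated CRP, then nr-axSpA with elevated and non-elevated CRP. The smallest cell has 4 patients per arm. The factor levels have 10 + 4 = 14 and 22 + 16 = 38 for radiographic status, and 10 + 22 = 32 and 4 + 16 = 20 for CRP. Both main effects can be estimated despite the thin cell.

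**The case against.** The strongest reply is that nothing vital is at risk. The trial was sized without stratification, the exact fallback keeps 90.6% power, and any error works against the sponsor's own claim. All of this stands. A reader might infer that the fallback leaves the trial underpowered; the figures do not support that.

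Other stronger readings also fail:

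- *The fallback will probably be used.* No expected share of r-axSpA or of elevated CRP is given, so this is conjecture.
- *The choice would be made on unblinded data.* The article does not say so, and stratum counts can be read without treatment codes or outcomes.
- *The lack of a number for a sufficient stratum is a gap.* The analysis plan, which is not shown, may supply it. The point here is the rule that the article does fix, which leads to an unadjusted analysis whatever the number.
- *The whole excess width comes from dropping strata.* In the worked example, the 5 to 7% comes from exactness.
- *A stratified analysis always does better.* Mehrotra-Railkar ranged from 89.6 to 92.5% power across assumed settings, and was up to about 1 point below Chan-Zhang when strata were not prognostic. The comparator in the table is CMH.

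The ANCOVA sentence names the factor in the singular and may mean one four-level term. Coding it as two main effects is therefore a recommendation. The repeated-measures sentence uses the plural.

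**Conclusion.** The point holds as a contradiction and an avoidable inefficiency; it does not threaten the trial's validity. The unconditional promise of an adjusted interval cannot be met in the fallback branch, and this does not depend on any assumption.

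The loss depends on stratum shares and prognostic strength that the article does not give. Under assumed values:

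- **Primary endpoint:** about 0 to 2.5 points of power (2.7 in the most extreme setting), with the fallback always above 90%, and a two-sided type I error of about 3 to 5%. The low end of that error needs strongly prognostic strata.
- **Key secondary ANCOVA:** an interval about 3 to 5% wider if the factors explain 5 to 10% of residual variance.
- **Strata not prognostic:** essentially no loss.

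**What to change.** 1. In the ANCOVA and the repeated-measures model, keep radiographic status and CRP status as two main effects in all cases and delete the condition.
2. For the primary and binary secondary endpoints, replace the unstratified fallback with a stratified one. Either collapse sparse strata in a fixed order, decided on blinded pooled counts, or use CMH-type weights, which tolerate small strata. Keep Chan-Zhang as a sensitivity analysis.
3. The adjusted-interval sentence can then stand as written, because every branch delivers such an interval.

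This changes wording only, with no new data or patients. The statistical cost is a very small loss of power if the strata turn out not to be prognostic: under about 1 point, depending on the weights.

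### The as-observed sensitivity analysis of the primary endpoint changes the handling of escalated patients along with that of dropouts, so it is only a weak check of the missing-data assumption

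*Protocol article*

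**What the plan says.** All references are to the Protocol article.

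- **Escalation (Study population and design).** Patients in either arm whose BASDAI at week 4 is still at least 4 and has improved by less than 20% move to open-label tofacitinib 5 mg BID until week 16.
- **Assessment (Table 2).** ASDAS is scheduled at baseline, week 4 and week 16, with no exception for escalated patients.
- **Primary rule (Statistical analysis).** Patients are analysed as randomised. One sentence covers three kinds of event: "Missing values from patients who drop out or receive prohibited medication or treatment escalation for any reason before week 16" are set to non-response.
- **Sensitivity analysis (same section).** "For sensitivity analysis, the above analysis will be repeated using data as observed without missing imputation".
- **Binary secondary endpoints (same section).** For these, "the same analysis as defined in primary analysis and corresponding sensitivity analysis will be applied accordingly".
- **Key secondary endpoint (same section).** Here the plan does say what happens to data collected after prohibited medication or escalation: they are excluded. No such statement accompanies the sensitivity analysis of the primary endpoint.

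**The concern.** A sensitivity analysis for missing data should hold the question fixed and vary only what is assumed about the values that were not obtained. Here a single non-responder rule does two jobs. It fills in outcomes for patients who left, and it defines escalation as failure for patients who stayed and were measured. Removing it undoes both.

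For an escalated patient who attends week 16, two readings of the as-observed run are open:

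- **Kept.** The observed ASDAS counts. A placebo patient who has had about 12 weeks of open-label tofacitinib contributes that result to the placebo arm.
- **Dropped.** The patient leaves the analysis because of a week-4 failure that treatment is expected to influence. The plan itself treats the share escalated as an efficacy endpoint. The groups compared are then no longer the randomised ones.

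Under either reading, a gap between the primary and sensitivity results could not be put down to the non-responder assumption for dropouts. A sound primary result could look fragile because placebo patients received tofacitinib, or look confirmed or enlarged because early failures were removed. The same ambiguity passes to the week-16 binary secondary endpoints, such as ASDAS <2.1, ASAS20, ASAS40, partial remission and BASDAI50.

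**Working it through.** **Step 1: reproduce the planned figure.** The Sample size section says "we anticipate that 20% in the placebo (+naproxen) group and 50% in the tofacitinib (+naproxen) group will achieve remission", that "a total of 104 subjects will be randomly assigned to one of the arms" 1:1, and that this is "with a power of 90% and two-sided alpha of 0.05". With the pooled-variance formula and no continuity correction:

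n per arm = [1.960 × √(2 × 0.35 × 0.65) + 1.282 × √(0.20 × 0.80 + 0.50 × 0.50)]² / 0.30² = (1.322 + 0.821)² / 0.09 ≈ 51.0, rounded up to 52.

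The total is 104, which matches. Power at 52 per arm is 90.6%. The sample size is not in question.

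**Step 2: assumptions for the illustration.** The article gives no escalation rates and no remission rates after escalation, so these are assumed:

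| | Placebo | Tofacitinib |
|---|---|---|
| Primary result, escalated = non-responders | 20% | 50% |
| Share escalated at week 4 (e) | 30-40% | 10-20% |
| Remission at week 16 among escalated (q) | 30-50% | 10-15% |

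Holding the primary result at 20% and 50% is also an assumption. The Sample size section anticipates these rates without saying how escalated patients were counted in them. Dropout is set to zero here to isolate escalation.

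**Step 3: escalated patients kept.** Observed rate = primary rate + e × q.

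- Placebo: 0.20 + 0.30 × 0.30 = 0.29, up to 0.20 + 0.40 × 0.50 = 0.40.
- Tofacitinib: 0.50 + 0.10 × 0.10 = 0.51, up to 0.50 + 0.20 × 0.15 = 0.53.
- Difference: from 0.51 − 0.40 = 0.11 to 0.53 − 0.29 = 0.24.

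**Step 4: escalated patients dropped.** Observed rate = primary rate / (1 − e).

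- Placebo: 0.20 / 0.70 = 0.286, up to 0.20 / 0.60 = 0.333, on about 36 down to 31 of 52 patients.
- Tofacitinib: 0.50 / 0.90 = 0.556, up to 0.50 / 0.80 = 0.625, on about 47 down to 42 of 52 patients.
- Difference: from 0.556 − 0.333 = 0.222 to 0.625 − 0.286 = 0.339.

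**Step 5: a central case.** With 35% and 15% escalated, and 40% and 15% of those remitting:

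- Kept: 0.20 + 0.35 × 0.40 = 0.34 versus 0.50 + 0.15 × 0.15 = 0.52, about 18 points.
- Dropped: 0.20 / 0.65 = 0.31 versus 0.50 / 0.85 = 0.59, about 28 points.

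**Step 6: dropout alone, for comparison.** The plan expects little of it: "Considering low historical drop-out rates, the sample size will not be adjusted for the drop-out rate". With no escalation and 5-10% dropout per arm, omitting dropouts instead of failing them gives:

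| Dropout, placebo / tofacitinib | Placebo rate | Tofacitinib rate | Difference (points) |
|---|---|---|---|
| 10% / 5% | 0.20 / 0.90 = 0.222 | 0.50 / 0.95 = 0.526 | 30.4 |
| 5% / 5% | 0.20 / 0.95 = 0.211 | 0.50 / 0.95 = 0.526 | 31.6 |
| 10% / 10% | 0.20 / 0.90 = 0.222 | 0.50 / 0.90 = 0.556 | 33.3 |
| 5% / 10% | 0.20 / 0.95 = 0.211 | 0.50 / 0.90 = 0.556 | 34.5 |

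The component the sensitivity analysis should probe moves the 30-point difference by less than 5 points. With escalated patients kept, the shift is 6-19 points downward. With them dropped, it runs from about 8 points down to 4 points up.

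**The case against.** - **It still tests something.** Moving a dropout from certain failure to omitted does change the assumption about truly missing values. This stands. For dropouts who never escalated, the run is a crude complete-case check, so a reader who inferred that it tests nothing would go too far.
- **The kept reading is coherent.** Counting all week-16 data by randomised arm is a treatment-policy comparison. If placebo patients escalate more often, it usually dilutes the difference, so a positive result would be supportive. This also stands, but it answers a different question from the primary analysis and should carry its own name. A diluted result would not contradict the primary one.
- **The primary rule is already clear.** Escalation is named in the non-responder sentence, so the intent is not in doubt even though that sentence speaks of missing values and an escalated patient's ASDAS is normally observed. For the primary analysis this is a wording repair only. A reader might infer that the primary analysis is flawed, and the text does not support that.
- **There may be a third reading.** Escalated patients might stay non-responders while only dropouts are omitted. That would be a cleaner check, but the article does not say it, and removing the imputation points the other way.
- **Other analyses may exist.** A reader might infer that this is the trial's only sensitivity analysis of the primary endpoint. That is true of the article alone. The full protocol or SAP, which is not shown, may contain more. The point here concerns the analysis that is stated, not the absence of others.
- **Dropout is expected to be low, so a better missing-data analysis may show little.** This is fair. It is also why the as-observed run would mostly report on escalation.

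**Conclusion.** The concern holds in limited form. As written, the sensitivity analysis of the primary endpoint, and with it those of the binary secondary endpoints, changes the treatment of escalation and of dropout at the same time. It is a weak complete-case check of the dropout assumption, and a departure from the primary result would mostly reflect how escalated patients were handled. Against 30 points planned, the illustration gives about 11-24 points if they are kept and about 22-34 points if they are dropped. These ranges rest wholly on the assumed escalation and open-label remission rates and on a primary result fixed at 50% versus 20%. That one rule covers both kinds of event, and that post-escalation data are addressed only for the key secondary endpoint, follows from the text and needs no assumption. The primary analysis and the sample size stand. The plan should be corrected before unblinding.

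**What to change.** In Statistical analysis:

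1. Reword the non-responder rule so that escalation or prohibited medication before week 16 counts as non-response whatever week-16 ASDAS is observed, in both the primary and the sensitivity analysis. Treat missing week-16 ASDAS in a separate sentence.
2. Replace the as-observed run with one that varies only truly missing week-16 ASDAS: multiple imputation from baseline and earlier ASDAS, BASDAI and CRP, all of which are already scheduled, and a tipping-point table over the number of remitters among the missing in each arm.
3. If an analysis that keeps post-escalation data is wanted, list it as a separate treatment-policy estimate, not as a sensitivity analysis for missing data.
4. Carry the same wording to the binary secondary endpoints.

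The cost is a few sentences, a small table and a little extra analysis work. Sample size, data collection and clinical procedures are unchanged. If the full protocol or SAP already defines such analyses, only the wording needs to be aligned.
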